## Abstract

**Introduction::**

Microsurgical clipping and endovascular coiling are the main methods against unruptured intracranial aneurysm (UIA). The craniotomy of surgical clipping may increase the risk of cerebrospinal fluid leakage and infection, damage the brain tissue, produce excessive stimulation to the nerves and blood vessels around the aneurysm, and cause the corresponding neurological deficit. Endovascular coiling could significantly reduce the mortality and disability rate than surgical clipping technique, which made endovascular coiling to become the first choice for the treatment of UIA. However, the long-term results showed attenuated favorable outcomes of coiling over clipping, so it is still in debate whether to clip or to coil. Therefore, we try to conduct a randomized, controlled, prospective trial to assess the long term safety of endovascular coiling therapy against UIA compared with microsurgical clipping technique.

**Methods::**

Parallel-group randomization (1:1) is generated through the random number generator in Microsoft Excel 2010. In this trial, blinding to patients, physicians, and outcome assessors is not possible. Endovascular coiling or surgical clipping will be performed once for each patient in treatment group or control group, respectively. The mRS, overall mortality rate, disability rate, morbidity rate, and occurrence of a major aneurysm recurrence measured at 6 month and 1 year will be recorded.

**Conclusions::**

The findings will be helpful for the choice of endovascular coiling or surgical clipping by assessing the long term efficacy and safety of both operations against UIA.

**Trial registration::**

OSF Registration number: DOI 10.17605/OSF.IO/QYE9F.

## Introduction

1

Intracranial aneurysm (IA), also known as cerebral aneurysm, is a localized dilation or ballooning in the cerebral vasculature due to the weakness in the wall of blood vessel.^[1,2]^ The prevalence of unruptured IA (UIA) is 7% in China,^[3]^ and an estimated occurrence of 3.2% worldwide.^[4]^ Most UIAs remain asymptomatic through life, but the ruptured aneurysms causing subarachnoid hemorrhage will lead to severe headache, loss of consciousness, seizure, and even life threat. Many ruptures are fatal, and of the patients who survive, approximately 50% will develop serious complications.^[5]^ Therefore, early surgical intervention is important to reducing mortality and disability.

Microsurgical clipping and endovascular coiling are the main methods against IA.^[6]^ The technique of microsurgical clipping has a long history,^[7]^ and it can open the subarachnoid, release bloody cerebrospinal fluid, and reduce the incidence of cerebral vasospasm.^[8]^ Microsurgical clipping remained to be the preferred operation for its advantages of high aneurysm clipping rate and prevention of rerupture bleeding. However, the craniotomy may increase the risk of cerebrospinal fluid leakage and infection, damage the brain tissue, produce excessive stimulation to the nerves and blood vessels around the aneurysm, and cause the corresponding neurological deficit.

Endovascular coiling therapy emerged in the 1990s with the development of detachable coil system.^[9–11]^ It is a minimally invasive technique without a craniotomy, which could greatly reduce the pain of the patient and makes it easier to be accepted.^[12]^ An 18-year-follow-up study of the International Subarachnoid Aneurysm Trial (ISAT) showed that endovascular coiling could significantly reduce the mortality and disability rate than surgical clipping technique, which made endovascular coiling to become the first choice for the treatment of UIA. ISAT also demonstrated that that the rerupture bleeding rate of endovascular therapy is higher than that of surgical clipping technique,^[13]^ and the long-term results showed attenuated favorable outcomes of coiling over clipping,^[14,15]^ so it is still in debate whether to clip or to coil.^[16]^ Therefore, we try to conduct a randomized, controlled, prospective trial to assess the long term efficacy and safety of endovascular coiling therapy against IA compared with microsurgical clipping technique.

## Methods

2

### Study design

2.1

The study will be conducted at hospital, and it is a randomized, controlled clinical trial. A flowchart is shown in Figure 1. The study conforms to the SPIRIT 2013 Statement. The protocol will be in accordance with the Helsinki Declaration and approved by the Health Research Ethics Board of our hospital. This experiment has been registered in the open science framework (OSF) (registration number: DOI 10.17605/OSF.IO/QYE9F). Before randomization, all patients will sign a written informed consent and they can freely choose whether to continue the trial at any time.

**Figure 1 F1:**
[figure not shown]
Flow diagram of the study.

### Participants

2.2

Participants’ identification, recruitment, and consecutive enrollment will be all performed in our hospital. Inclusion criteria for participants are: being aged between 18 and 80 years old; having one IA within the anterior circulation, and being considered appropriate for both surgical and endovascular management; exclusion criteria comprise: multiple untreated IAs; an acutely ruptured aneurysm within 14 days of enrollment; modified Rankin Scale (mRS) score of ≥4 or Hunt and Hess score ≥3; cerebral vascular malformation or intracranial mass; a history of ischemic stroke, nervous system tumors, Alzheimer disease, or mental illness.

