### Sample size

2.6

With alpha 0.05, power 80%, loss to follow-up 20%, and the estimated 18% and 30% of poor clinical outcome rates at 6-month follow-up for endovascular coiling and surgical clipping respectively, a sample size of 450 will be needed.

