## Discussion

3

Most IAs are clinically silent, and the rupture is unpredictable and associated with hematoma and hemorrhage. With the ongoing advances and widespread use of imaging techniques, the possibility to detect asymptomatic aneurysm has increased significantly.^[17]^ The etiology of IA has not yet been clearly defined, and it is mainly believed to be related to congenital arterial wall defects, increased intravascular pressure, atherosclerosis, and vasculitis.^[18,19]^ Treatment of unruptured IAs is still being discussed. Endovascular therapy has become the main method for the treatment of UIA with the advantages of low fatality and disability rate.^[20–23]^ However, it is still controversial about the choice of endovascular coiling because the long term outcomes are still in debate.^[14,15]^ In order to be helpful for the choice of endovascular coiling or surgical clipping, we try to conduct the study to assess the long term efficacy and safety of both operations against UIA. Additionally, this research includes only patients in 1 hospital in China, and the conclusions will be more limited to Chinese people. And the not applicable blind method will also lead to certain biases for the results.

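### The stated question is about unruptured aneurysms, but the eligibility criteria do not require the study aneurysm to be unruptured, and the two must be reconciled

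*Protocol article*

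**What the plan says.** The target population is stated four times, in two ways.

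- Abstract, Introduction: the aim is "to assess the long term safety of endovascular coiling therapy against UIA compared with microsurgical clipping technique".
- Abstract, Conclusions: the findings will guide the choice of operation by "assessing the long term efficacy and safety of both operations against UIA".
- Discussion: the study is run "to assess the long term efficacy and safety of both operations against UIA".
- Section 1 (Introduction), last sentence: the aim is to assess the "long term efficacy and safety of endovascular coiling therapy against IA compared with microsurgical clipping technique".

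The population to be enrolled is set in section 2.2 (Participants). The aneurysm criterion for inclusion is "having one IA within the anterior circulation, and being considered appropriate for both surgical and endovascular management". The exclusions include more than one untreated aneurysm, "an acutely ruptured aneurysm within 14 days of enrollment", and "modified Rankin Scale (mRS) score of ≥4 or Hunt and Hess score ≥3". Nothing elsewhere in the article limits enrolment to unruptured aneurysms.

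**The concern.** Eligibility decides whom the estimate describes. The Abstract and Discussion promise an answer for UIA, but the criteria let in a single anterior-circulation aneurysm whether or not it has bled, provided any acute rupture lies outside the 14-day window. A site that follows section 2.2 literally could enrol patients treated electively together with patients recovering from a haemorrhage.

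The primary outcomes in section 2.5 include mRS, mortality and disability at 6 months and 1 year. In a patient who has bled, these may partly reflect the earlier bleed, and the difference between coiling and clipping may not be the same as in a patient who has not. The pooled comparison would then answer a question about a mixture, while the conclusion is worded for one component of it. Restricting the analysis to unruptured cases afterwards would leave fewer patients than the 450 planned in section 2.6.

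**Working it through.** No figure in the article measures this point, so the check sets the passages side by side.

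**1. Does IA in section 2.2 mean UIA?** Section 1 defines IA as any localised dilation of a cerebral vessel and introduces UIA as the unruptured kind, with its own prevalence figures. The two abbreviations are distinct, so IA in the inclusion criterion cannot simply be read as UIA.

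**2. Does an exclusion supply the missing restriction?** The only clause that names rupture covers the 14 days around enrolment. An aneurysm that ruptured earlier is not caught by it. The mRS and Hunt and Hess limits bear on the patient's condition: mRS of 4 or more is excluded, so 0 to 3 remains eligible, and Hunt and Hess of 3 or more is excluded, so lower scores remain eligible. Neither limit requires an unruptured aneurysm.

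**3. Does the rest of the article settle it?** Three statements (Abstract objective, Abstract conclusion, Discussion) say UIA. One (the objective at the end of section 1) says IA and agrees with section 2.2. The background in section 1 also mixes the two: it argues for a UIA trial partly from a trial in subarachnoid aneurysms, from rates of repeat bleeding, and from the clearing of blood-stained cerebrospinal fluid at surgery. The planning rates in section 2.6 (18% and 30% poor outcome at 6 months) are not attached to either population, so they do not settle it.

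**4. What would a mixture do to the estimate?** Let r be the share of enrolled patients with an earlier rupture, D_u the risk difference in unruptured patients and D_r the risk difference in previously ruptured patients. With 1:1 randomisation, r is the same in both arms in expectation, so

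pooled difference = (1 − r) × D_u + r × D_r,

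and its departure from the UIA effect is

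pooled difference − D_u = r × (D_r − D_u).

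This is zero if r = 0 or if the two effects are equal. Otherwise its sign is that of D_r − D_u and its size grows with r. The article gives none of r, D_u or D_r. On the wording, r may lie anywhere from 0 upwards with no stated limit, and the departure may go either way.

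**The case against.** The strongest reply is that the 14-day and Hunt and Hess clauses may not concern the study aneurysm at all. Section 2.2 excludes multiple untreated aneurysms, which suggests that a patient may have another aneurysm that has already been treated. Both clauses can be read as covering a bleed from that other aneurysm, with the study aneurysm tacitly unruptured. This stands to the extent that a reader might infer from these clauses that the trial means to enrol ruptured study aneurysms, and the article does not show that. The solid evidence is the inclusion criterion, which lacks any reference to rupture status, and this alternative reading does not supply one.

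A second reply is that the Introduction's own objective says IA, so eligibility agrees with one of the stated aims. This also stands. It means the fault is a contradiction about which population is intended, and it cannot be assumed that the eligibility section is the part in error.

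A third reply is that allocation is randomised, so the comparison between arms is sound for whoever is enrolled. That is correct. The consequence is for the population label and applicability, not for the internal validity of the comparison.

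That the article is condensed is not an answer here. The eligibility criteria are given, and the point is what they say against the stated aim.

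**Conclusion.** The point holds as a contradiction between the stated target population and the eligibility criteria. As written, the criteria permit patients whose study aneurysm ruptured more than 14 days before enrolment. If any are enrolled, the pooled result could not be reported as a UIA result, which is how the Abstract and Discussion intend to use it.

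Its size is unknown. The conclusion rests on the wording alone and assumes only that sites may apply section 2.2 literally. A reader might go further and infer that a substantial ruptured share will be enrolled, or that the UIA effect will be overstated by some percentage. The documents support neither: they give no share and no effect by rupture status, and even the direction of any distortion would have to be assumed.

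It should still be settled before enrolment, because the criteria determine the population and a later restriction would cost sample size.

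**What to change.** Reconcile the Abstract (objective and conclusion), the Introduction's objective, section 2.2 and the Discussion so that all name the same population. There are two ways, and the choice is the sponsor's.

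- **Restrict to unruptured aneurysms.** Add unruptured to the inclusion criterion for the study aneurysm and bring the Introduction's objective into line. Keep the 14-day and Hunt and Hess exclusions in view: the sponsor should state whether they apply to bleeds from another aneurysm. Simply deleting them could admit patients with a recent bleed from a different, treated aneurysm. Cost: a short amendment and possibly slightly slower recruitment.
- **Keep the present criteria.** State the objective and conclusion for intracranial aneurysm in the Abstract and Discussion, record rupture history of the study aneurysm at baseline, and report the primary outcomes separately by it as well as overall. Cost: rewording, one baseline item and one set of tables. The separate estimates will each be less precise than the overall one.

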### Randomization and blinding

2.3

Parallel-group randomization (1:1) is generated through the random number generator in Microsoft Excel 2010. In this trial, blinding to patients, physicians, and outcome assessors is not possible.

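### Section 2.3 states how the sequence is generated but not how the next allocation stays hidden until the judgement-based entry decision is recorded, and section 2.7 leaves known baseline risk unadjusted

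*Protocol article*

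**What the plan says.** All references are to the protocol article.

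- **Allocation (section 2.3, repeated in the abstract).** "Parallel-group randomization (1:1) is generated through the random number generator in Microsoft Excel 2010". The text names a ratio and a tool. It names no list holder, no point at which the list is fixed and no release step.
- **Blinding (section 2.3).** "blinding to patients, physicians, and outcome assessors is not possible". The Discussion accepts that this will bias results to some degree.
- **Recruitment (section 2.2).** Participants' "identification, recruitment, and consecutive enrollment will be all performed in our hospital".
- **Entry (section 2.2).** A patient must have one anterior-circulation aneurysm and meet the condition of "being considered appropriate for both surgical and endovascular management".
- **Baseline risk (section 2.2).** An mRS of 4 or more is excluded, so 0 to 3 can enter. Rupture is excluded only when it falls within 14 days of enrolment, so an older rupture is not excluded.
- **Consent and reporting standard (section 2.1).** "Before randomization, all patients will sign a written informed consent", and "The study conforms to the SPIRIT 2013 Statement".
- **Outcomes and analysis (sections 2.5 and 2.7).** mRS is one of the primary outcomes. The methods listed are two-group tests without covariates: chi-square, Fisher, t and rank tests.

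**The concern.** Producing a random sequence and concealing it are separate safeguards, and section 2.3 states only the first. Concealment matters more here than in most trials, because the treatment is open, assessors are unblinded, and the main entry criterion leaves room for discretion. Someone who knew that the less favoured arm came next could judge a difficult patient unsuitable for one of the procedures, and the record would show an ordinary screening failure. That kind of selection would affect every primary outcome. If it acted on features that were not recorded, no analysis could remove it.

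The second part concerns section 2.7. Baseline mRS is measured on the same scale as a primary outcome, and both it and an earlier rupture are known before allocation. Unadjusted tests make no use of that information. They lose precision, and they leave any difference between the arms in these factors, from whatever cause, in the estimate.

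**Working it through.** **The plan's own figure.** The article gives no number for concealment or balance, so there is nothing to reproduce on this point. The total of 450 is taken as stated. Whether it follows from its own inputs is a separate matter.

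**Inputs from section 2.6.** Poor outcome 18% with coiling and 30% with clipping, a planned difference of 12 points; total 450; loss to follow-up 20%. Evaluable per arm: 450 × 0.80 / 2 = 180. Mean risk: (18% + 30%) / 2 = 24%.

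**Step 1: what is stated at each stage.** Identification and the suitability judgement come first, then consent, then randomization. The article places consent before randomization. It does not say that the suitability judgement must be recorded before anyone can learn the allocation, or who can learn it. Consent before randomization would not by itself stop an unsuitability call made before consent by someone who knew what came next.

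**Step 2: size if high-risk patients were diverted (illustration).** Assumptions, none of them in the article: a share h of clipping candidates is high risk with a 50% poor-outcome rate, the overall clipping rate is the planned 30%, and a fraction d of the high-risk patients is turned away when clipping is next.

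Clipping rate among those who remain = (0.30 − d·h·0.50) / (1 − d·h)

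| h | d | Calculation | Clipping rate | Shift |
|---|---|---|---|---|
| 10% | all | (0.30 − 0.05) / 0.90 | 27.8% | 2.2 points |
| 20% | all | (0.30 − 0.10) / 0.80 | 25.0% | 5.0 points |
| 10% | half | (0.30 − 0.025) / 0.95 | 28.9% | 1.1 points |
| 20% | half | (0.30 − 0.05) / 0.90 | 27.8% | 2.2 points |

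In this direction the planned 12-point difference would shrink to between 10.9 and 7.0 points. Diversion away from coiling would push it the other way.

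**Step 3: effect of such a shift on the test (illustration).** Take no true treatment effect, 180 per arm, mean risk 24%, and a selection-induced risk difference b, so p1 = 0.24 − b/2 and p2 = 0.24 + b/2.

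- Critical difference c = 1.96 × √(2 × 0.24 × 0.76 / 180) = 0.088
- Standard error s = √{[p1(1 − p1) + p2(1 − p2)] / 180}
- Two-sided rejection rate = Φ(−(c − b)/s) + Φ(−(c + b)/s)

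For b = 0.04, s = 0.045, and the rate is 14.4%.

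| b (points) | 0 | 2 | 4 | 6 | 8 |
|---|---|---|---|---|---|
| Rejection rate | 5.0% | 7.3% | 14.4% | 26.5% | 42.7% |

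**Step 4: chance imbalance, kept separate.** If allocation is a simple draw of 450, a baseline factor present in 20% of patients (assumed) differs between the arms by up to 1.96 × √(0.2 × 0.8 × 4 / 450) = 7.4 points over the 95% range. This is imbalance in a covariate. With the Step 2 risks at h = 20% (50% in the high-risk group, 25% in the rest), it moves the outcome difference by 0.074 × 0.25 = 0.0185, a little under 2 points. It is not bias, because the significance level already allows for it. Covariate adjustment would remove much of it.

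**The case against.** The strongest reply is that this is a condensed article, and the mechanics of concealment are commonly left to the full protocol. The article claims SPIRIT 2013 conformity, describes enrolment as consecutive and puts consent before randomization. Consecutive enrolment bears directly on selective exclusion.

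Much of this stands. A reader might infer that the method gives no protection, that recruiters can see the list, or that a spreadsheet draw can be repeated until it suits. The documents support none of these. They do not say who holds the list, which Excel function is used or whether the values are fixed once drawn. A list made in Excel, locked and held independently, would be acceptable. If the sequence is unblocked, past assignments say nothing about the next one, so foreknowledge would need access to the list. The 7.4-point figure should not be set beside selection bias as if it were the same thing.

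The objection also applies to the usual remedy. Permuted blocks within strata can make late-block assignments easier to guess in an open single-hospital trial, and simple randomization is valid at this size.

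It does not remove the whole point. Neither consecutive enrolment nor prior consent hides the next allocation, and a claim of SPIRIT conformity is not a description of concealment. The unadjusted tests in section 2.7 are written down as the plan, so that part does not rest on silence. Those tests are valid under sound randomization; the criticism is that they pass over information already in hand.

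**Conclusion.** The point holds in a limited form. Section 2.3 as written covers sequence generation alone, and nothing in the stated procedure keeps the next allocation hidden until the dual-suitability judgement is recorded, in a trial where open treatment and discretionary entry make that step important. Section 2.7 commits to unadjusted tests although baseline mRS, and earlier rupture where present, are known at entry. That baseline mRS and earlier rupture predict outcome is an assumption, though a natural one for mRS, which is also a primary outcome.

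The size is conditional. Shifts of 1.1 to 5.0 points follow from assumed high-risk shares of 10% to 20%, a 50% event rate and diversion of half to all such patients. They show what a failure of concealment could cost and give no evidence that one is planned or likely. The inference that the arms can be filled selectively goes beyond the text. This is an inexpensive improvement worth making before enrolment, not a demonstrated flaw in the allocation.

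**What to change.** **Section 2.3.** State that the list is generated and locked before the first patient is enrolled; that it is held by an existing colleague who neither recruits nor treats; and that allocations are released one at a time, each only after consent, the dual-suitability judgement and baseline mRS are recorded. Excel may stay as the generating tool. If the full protocol already contains these steps, one sentence here to say so is enough.

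**Section 2.7.** Adjust the primary mRS or poor-outcome comparison for baseline mRS, and for earlier rupture if such patients remain eligible. Adjustment improves precision and deals with imbalance in these measured factors. It does not replace concealment, because it cannot correct selection on unrecorded features.

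**Optional.** Stratify the randomization by the same factors. If blocks are used, vary their sizes and do not disclose them, because of the guessing problem described above.

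**Cost.** Slightly more administration at enrolment and a little more analysis work, with no additional patients or visits. The allocation steps must be in place before enrolment starts.
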